### Standard care arm

2.10.

Participation in the trial will not affect access to palliative care, ethics, or other resources available at all study sites. Participants randomized to the usual care arm will receive communication and support at the discretion of the treating clinicians.

### Data collection

2.11.

We will establish baseline levels of surrogate psychological distress and unmet care needs, using the HADS and NEST scales [24,25]. We will also collect detailed demographic and disease data, frequency of multidisciplinary family meetings, bedside updates, palliative care consults, and encounters between the family and the social worker and pastoral care providers, gleaned from chart review. We will use web analytics to quantify how often surrogates accessed the FST and which sections of the tool they viewed. Primary and secondary outcome measures will be administered by phone or email to surrogates at 3 and 6 months. All outcome assessments will be blinded to ensure unbiased evaluation [25,26].

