Upon enrollment, surrogates will be oriented to the FST with a handout and with the study team. Surrogates in the intervention arm will receive unlimited access to the FST throughout hospitalization. Study staff will liaise with the enrolled surrogates and ICU team to schedule the first family meeting, within 2 days of enrollment (Table 1, Fig. 1). Family meetings may take place in person, via conference call, or via video meeting and must include the enrolled surrogates and ICU attending or their designee. Additional meeting participants will be at the discretion of the enrolled surrogates and attending. The tool was designed to be used sequentially in sections of approximately 25 min each, yet with time periods for reflection and processing interspersed. In addition, family members can review any useful sections at any time. Surrogates will be prompted to use the tool upon enrollment (section 1: about the ICU), and before the first clinician-family meeting (section 2: getting ready to talk to the healthcare team, section 3: your loved one’s values and treatment options). The study team will monitor completion and prompt family members as needed. After completing the FST, the study team will provide surrogates and ICU team members with a brief summary report containing information provided by the surrogates, such as their main questions, their preferred decision-making role, their loved one’s health-related values, their prognostic expectations and their understanding of their loved one’s treatment preference (i.e., toward life-extending care, a trial of life-extending care, or comfort-focused care). The study team will briefly review the summary with clinicians, which prompts them to address key elements of shared decision-making.

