If the patient remains in the ICU on study day 5, study staff will liaise with surrogates and the ICU team to schedule the second family meeting, to take place on days 5–9 of enrollment. At least 24 h before the second scheduled family meeting, the study staff will assign the surrogates FST section 4: getting ready for your next meeting with the healthcare team. Study staff will similarly monitor surrogates’ progress and provide support for completion. On study day 5, the surrogates and ICU staff will be administered the day 5 survey (which takes 10–15 min), via REDCap, or administered by staff, assessing their understanding of their loved one’s prognosis, their opinions on the communication, the FST, and on their own decision-making. The clinician participating in the patient’s final family meeting (whether it is meeting 1 or meeting 2) will complete a brief survey (5–10 min) sharing their perspective on the patient’s clinical case and prognosis, as well as their opinions on the FST. If the patient remains in the ICU after the second family meeting, a weekly family meeting will be scheduled within 5–9 days of the previous meeting.

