### Outcomes

2.12.

We will measure the intervention’s effect on four domains of outcomes: patient clinical outcomes, surrogates’ long-term psychological outcomes, decision/communication quality, and end-of-life healthcare utilization. The primary outcome is patient centeredness of care, measured at 3-month follow-up using the 12-item Patient-Perceived Patient-Centeredness of Care Scale (PPPC) modified for surrogates [26–28]. Secondary outcomes are summarized in Table 2.

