To establish and maintain intervention fidelity in this efficacy trial, we developed a rigorous and multifaceted intervention fidelity monitoring plan according to recommendations from the NIH Behavior Change Consortium. In addition, in a novel approach to intervention fidelity monitoring, we took advantage of an interactive, virtual tool being part of this intervention, and built intervention fidelity monitoring components into its design. In this way, study staff will receive real-time accurate feedback about surrogate progress on the FST, allowing for timely interventions from them to increase fidelity. Study staff themselves participated in planning and coordinating interdisciplinary family meetings at the set meeting times, in addition to nudging clinical teams and surrogates to complete their parts in the intervention. We also used more standard methods of IFM, following approaches that we have used in the past, which have allowed us to achieve greater than 95% fidelity to a complex behavioral intervention in past clinical trials [44,45]. These processes included: 1) multimodal orientation and training of interventionists, 2) detailed fidelity monitoring using a combination of clinician-reported checklists and chart review, and 3) ongoing feedback and support of clinical teams.

One limitation is that we do not have attention control. Therefore, we cannot exclude the possibility that any positive effect might be due not to the specific active ingredients of the digital intervention, but to the higher degree of interaction with research staff to help onboard them to the study. We think this is exceedingly unlikely given that the research staff will not be trained to deliver emotional support and will be instead trained to be research coordinators.

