€ Ottawa Decision Support Framework: tools to assess decisional needs, provide decision support interventions, and evaluate decision outcomes [18].

**Table 2 T2:** Outcome domains and the methods through which each will be assessed. ICU = Intensive Care Unit.

Domain	Instrument	Data source	Timepoint for collection
Patient Clinical Outcomes, Measures of Patient Centeredness of Care	Patient-Perceived Patient-Centeredness of Care Scale (PPPC)*	Surrogate (s)	3 months
	Needs of Social Nature, Existential Concerns, Symptoms, and Therapeutic Interaction (NEST)‡	Patient, surrogate (s)	Hospitalization Day 5
	Goal concordance of care^¶^	Surrogate (s)	3 months
	Quality of Death and Dying (QODD)^†^	Surrogate (s)	6 months
	Survival to discharge	Chart abstraction	6 months
	Duration of survival from enrollment to 6-months	Chart abstraction	
	Days alive at outside facility	Chart abstraction	
	Katz Index of Independence in Activities of Daily Living (patient’s functional status)^††^	Chart abstraction	
	Proportion of patients with comfort-focused care	Chart abstraction	
	Proportion of patients with new DNR during hospitalization	Chart abstraction	
	Proportion of patients enrolled in hospice during hospitalization	Chart abstraction	
	Time to hospice	Chart abstraction	
Surrogate Psychological Outcomes and ICU Experiences	Hospital Anxiety and Depression Scale (HADS)^‡‡^	Surrogate (s)	During admission
	Clinician-family conflict^₸^	Surrogate (s)	Hospitalization Day 2, Day 7
	Perceived effectiveness of FST^₸₸^	Surrogate (s)	Hospitalization Day 2, Day 7
	Family Satisfaction in the ICU (FS-ICU)^¶¶^	Surrogate (s)	3-months
	Impact of Events Scale-revised (IES-R, risk of post-traumatic stress disorder)^β^	Surrogate (s)	6-months
Patient Healthcare Utilization	ICU length of stay, hospital length of stay, duration of mechanical ventilation, index hospital costs	Chart abstraction	Throughout hospitalization
	Surrogate interviews to identify post-discharge encounters and costs	Surrogate (s)	Day 90, Day 180
Communication and Decision Quality	Clinician-Surrogate Concordance Scale (CSCS)***	Surrogate (s)	Hospitalization Day 2, Day 7
	Preparation for Decision-Making Scale^†††^	Surrogate (s)	Hospitalization Day 2, Day 7
	Decisional Conflict Scale (DCS), Decision Self-efficacy Scale^‡‡‡^	Surrogate (s)	Hospitalization Day 2, Day 7
	Quality of Communication (QOC) Scale**	Surrogate (s)	3-months

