* PPPC is a 12-item instrument that measures the patient-centeredness of care. It has been found to be one of the two best instruments to measure this construct, and has demonstrated validity and reliability when used by surrogates [26–28,39,40].

† QODD is a 19-item instrument with established psychometrics and successful use with ICU surrogates [46].

‡ NEST, or the adapted Needs of Social Nature, Existential Concerns, Symptoms, and Therapeutic Interaction [24,25] scale, is designed for ICU use; it is a 13-item instrument developed to identify unmet social, emotional, physical, and care-system needs in serious illness.

¶ Goal-concordance of care will be tested using an 8-item composite measure of goal-concordant care, in addition to the After-Death Bereaved Family Interview [3,47–49].

†† Patient functional status will be assessed using the Katz Index of Independence in Activities of Daily Living, a validated and widely-used scale [50].

‡‡ HADS is a 14-item assessment with subscales for anxiety and depression, with established reliability and validity among ICU surrogates that is recommended by consensus guidelines for use among ICU surrogates [32–35]. Each domain has a score range of 0–21 with the following interpretation: 0–7 normal, 8–10 borderline abnormal and 11–21, abnormal [32].

¶¶ Satisfaction with ICU care will be assessed using the Family Satisfaction in the ICU (FS-ICU) instrument at 3-month telephone follow-up of surrogates. The FS-ICU is a 24-item scale concerning satisfaction with care, communication, and decision-making in the ICU [15].

₸ A brief survey (measured by both surrogates and physician) will be used to determine the level of family-clinician conflict during index hospitalization.

₸₸ A brief survey asking (intervention only) participants about the perceived effectiveness of the FST intervention, during hospitalization.

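### The statement that all outcome assessments are blinded cannot hold for the surrogate-reported scales, including the primary outcome, and the article does not say who is masked.

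*Protocol article*

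**What the plan says.** Section 2.11 (Data collection) of the protocol article states: "All outcome assessments will be blinded to ensure unbiased evaluation". The sentence before it reads: "Primary and secondary outcome measures will be administered by phone or email to surrogates at 3 and 6 months".

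Section 2.12 (Outcomes) defines the primary outcome as the "12-item Patient-Perceived Patient-Centeredness of Care Scale (PPPC) modified for surrogates", measured at 3 months. Table 2 gives the surrogate as its data source.

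Section 2.5 (Intervention) says: "Surrogates in the intervention arm will receive unlimited access to the FST throughout hospitalization". Study staff also orient these surrogates, prompt them and arrange their family meetings. Section 2.10 leaves communication in the control arm to the treating clinicians. The Discussion concedes: "One limitation is that we do not have attention control".

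For the hospital stay, section 2.5 describes a day-5 survey for surrogates and ICU staff, completed "via REDCap, or administered by staff", whose topics include opinions on the FST. The footnotes to Table 2 add another instrument: "A brief survey asking (intervention only) participants about the perceived effectiveness of the FST intervention".

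**The concern.** On a self-report scale the respondent is the assessor. A surrogate who has worked through the FST and been invited to scheduled meetings knows that this happened. Masking an interviewer does not mask the person who answers, and when the scale comes by email there is no interviewer to mask.

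The sentence also claims a consequence, unbiased evaluation, which does not follow for a subjective rating by someone aware of the allocation. Gratitude or expectation could move PPPC scores without any change in care. If the sentence is carried into the results paper, readers could take a PPPC difference as masked evidence and give it more weight than the design supports.

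**Working it through.** **1. The text, by outcome type**

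- **PPPC and other surrogate scales at 3 and 6 months.** Rater: the surrogate (Table 2), by phone or email (section 2.11). Only intervention surrogates receive the FST (section 2.5), and no sham or attention control is described (Discussion). The article does not say outright that surrogates know their arm, but no other reading fits this design. Rater masking is not possible.
- **Telephone interviewers.** Section 2.8 describes a dedicated long-term follow-up team. Masking it is feasible, but the article does not say that it is done.
- **Chart-abstracted outcomes.** Abstractors could be masked; this too is not stated.
- **Day-5 survey.** It may be given by staff and asks about the FST (section 2.5). Study staff randomize (section 2.9), orient surrogates and schedule meetings (section 2.5), and the study team tracks FST progress (section 2.7). Section 2.5 does not say which staff give the survey or whether they are masked.
- **Clinician ratings.** A Table 2 footnote has the physician rate conflict as well as the surrogate. The ICU team receives the FST summary (section 2.5), so treating clinicians are not masked.
- **Perceived effectiveness of the FST.** Given in the intervention arm only, so its respondents cannot be masked.

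The word all therefore fails for the primary outcome and for several secondary ones.

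**2. What a reporting shift could do (illustration)**

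Inputs from the article: 370 patients, 20% loss to follow-up, 1:1 allocation, 1.5 surrogates per patient. The article's own figure reproduces: 370 × (1 − 0.20) = 296 patients, or 148 per arm. Surrogates per arm: 148 × 1.5 = 222.

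Assumptions, none of them in the article: two-sided alpha 0.05, no true effect, a pure reporting shift b in SD units, and a within-patient intraclass correlation (ICC) between 0 and 1.

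- Effective n per arm = 222 / (1 + 0.5 × ICC), treating cluster size as equal at 1.5.
- SE = √(2/n).
- Probability of significance = Φ(b/SE − 1.96) + Φ(−b/SE − 1.96).

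Worked case, ICC 1 and b = 0.10: n = 222/1.5 = 148; SE = √(2/148) = 0.1162; b/SE = 0.860; Φ(−1.100) + Φ(−2.820) = 0.138.

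| ICC | n per arm | b = 0.10 SD | b = 0.20 SD |
|---|---|---|---|
| 0 | 222 | 18.4% | 55.9% |
| 0.3 | 193 | 16.6% | 50.2% |
| 0.6 | 171 | 15.2% | 45.6% |
| 1 | 148 | 13.8% | 40.5% |

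For scale, the effect detectable with 80% power is 2.80 × SE: 2.80 × 0.0949 = 0.27 SD at ICC 0, and 2.80 × 0.1162 = 0.33 SD at ICC 1. Both assumed shifts are smaller than that.

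**The case against.** The strongest reply is that the sentence directly follows the one on 3- and 6-month follow-up, so it conventionally means that the people collecting those data are masked. The separate follow-up team makes this workable, and the article never says that participants are blinded. This may well be the intention. It is narrower than what is printed, however: it does not make a surrogate's own rating unbiased, and it does not reach the hospital surveys. Nor is this a detail that a condensed article leaves to the full protocol. It is a positive statement, and it is wrong as it stands.

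The Discussion's remark on attention control is related but different. It asks which ingredient of the intervention would explain a benefit, not whether unmasked respondents report differently.

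Several stronger readings are tempting, and the documents do not support them:

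- **The coordinators who support the intervention also give the day-5 survey.** The staff are not identified, so this is an inference from their other roles. The survey is also not the 3-month PPPC. Among the Table 2 outcomes only NEST is timed at day 5; conflict and the decision scales are listed at days 2 and 7. Which comparative outcomes the survey carries is therefore unclear.
- **The intervention-only survey biases the comparison.** It has no control counterpart, so it contradicts the word all but cannot distort a between-arm contrast.
- **The percentages estimate this trial's false-positive rate.** The shift has no source in the documents, and any assumed bias inflates the error rate. The figures restate the assumption.
- **The trial should have masked surrogates.** That is not feasible here, and nothing in this point asks for it.

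**Conclusion.** The point stands as a misstatement about masking that should be corrected. It is not a flaw that invalidates the design. The primary outcome and the other surrogate-reported scales are unmasked self-reports; the day-5 survey may be given by staff whose masking is not stated; and the Discussion does not list unmasked reporting as a limitation.

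No sample size, endpoint or other figure in the article changes. The size of any reporting bias is unknown. The illustration (about 14–18% for a 0.10 SD shift and 41–56% for 0.20 SD, across ICC 1 to 0) rests wholly on the stated assumptions. It shows only that a shift smaller than the detectable effect could matter.

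**What to change.** 1. Replace the blinding sentence in section 2.11. Say that the 3- and 6-month telephone interviewers and the chart abstractors are masked, if that is so, and that surrogates and treating clinicians are not.
2. Remove the assurance of unbiased evaluation for self-reported outcomes.
3. Report and interpret the PPPC as an unmasked self-report, beside the chart-abstracted outcomes, and add this to the limitations in the Discussion.
4. For hospital surveys that compare the arms, make the existing REDCap self-completion the default. Use staff administration as a fallback only and, where possible, by someone not supporting that family's intervention. Place the FST items last.

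Items 1 to 3 cost only wording and a less favourable masking claim. Item 4 needs no new system but carries some risk of more missing hospital surveys, since staff administration is now an open alternative; this is why it stays as a fallback. Item 4 does nothing for the PPPC itself, for which open description is the only remedy.

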### Outcomes

2.12.

We will measure the intervention’s effect on four domains of outcomes: patient clinical outcomes, surrogates’ long-term psychological outcomes, decision/communication quality, and end-of-life healthcare utilization. The primary outcome is patient centeredness of care, measured at 3-month follow-up using the 12-item Patient-Perceived Patient-Centeredness of Care Scale (PPPC) modified for surrogates [26–28]. Secondary outcomes are summarized in Table 2.

### Statistical analysis plan

2.13.

To assess the effectiveness of randomization, we will compare distributions of baseline characteristics for patients and surrogates between the two groups (FST intervention and standard care). For the superiority hypotheses (e.g., efficacy outcomes for the FST), all analyses will be performed under the intention to treat principle. We will follow best practice recommendations to perform non-inferiority analyses under the per-protocol principle. To compare the primary outcome between the two trial arms, we will employ linear mixed effect modeling. For each of the secondary outcome measures, depending on the distribution, a linear mixed effects model or a generalized linear mixed effects model with appropriate link function will be used to compare the difference between intervention groups. Likelihood ratio tests will be used for testing the intervention effect. To confirm our assumption of minimal clustering effects, we will calculate intraclass correlation coefficients for each outcome.

We conservatively estimate a 20% loss to follow up rate, meaning the total effective sample size will be 296 patients. All aforementioned power and sample size estimations are based on this effective sample size, with 1.5 surrogates per patient. For the analysis based on the per-protocol principle, an inverse-probability weighting method from the attrition model will be used. Baseline covariates and 3-month non-missing covariates will be included in the 3-month attrition model, while baseline, 3-month, and 6-month non-missing covariates will be included in the 6-month attrition model to maximize the accuracy of the estimation.

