Patient exclusion criteria include lack of surrogate decision maker, family not available for study, imminent death (within 24 h), goals of care already “comfort measures only,” decision for life support withdrawal already made, current participation in competing research study, incarceration or involuntary hold, death prior to enrollment, discharge prior to enrollment, regaining of capacity prior to enrollment, physician and/or designee declining participation, more than 5 days of ICU hospitalization. Surrogate exclusion criteria include being <18 years old, not having access to a device with internet capabilities, being unable to read or understand English, and having cognitive or physical limitations impacting ability to complete study questionnaires.

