Because the intervention is comprised of multiple components that work together to address multiple problems across multiple domains, we selected a wide range of outcomes. Specifically, we are interested in the intervention’s impact on patients’ clinical outcomes, surrogates’ psychological outcomes, decision and communication quality and end-of-life healthcare utilization, so we selected validated and responsive outcome measures to test hypotheses for each of these domains. The primary goal of this intervention is to increase the patient-centeredness of care, and the degree to which care aligns with patient goals. Thus, the primary outcome is a robust metric of patient centeredness of care, the PPPC, modified for surrogates [26,31–36]. We selected the PPPC because it has solid psychometric properties including responsiveness to change, and it is reported to be one of the best instruments to measure whether ICU care is tailored to patient individual values and preferences [26–28,37–41]. We selected 6-month survival as a safety outcome because we wish to address any concerns that robustly supporting surrogates facing EOL decisions might lessen survival over 6 months. Despite recent evidence that palliative approaches to care may prolong survival, some may fear the opposite is true [42,43]. We adequately powered the study to “rule out” increased mortality in the intervention arm through non-inferiority testing. We acknowledge that there is legitimate debate about whether a finding of shorter survival with better quality of dying in one arm would be a preferable outcome. Therefore, we believe our responsibility is to design our study to provide the data necessary to inform DSMB oversight and a broader public discussion.

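### The 6-month survival safety test is assigned to a per-protocol analysis with no all-randomised counterpart, although only the intervention arm has post-randomisation steps to adhere to, so selection could bias the safety conclusion

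*Protocol article*

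**What the plan says.** The Statistical analysis plan section (2.13) splits the analysis populations by type of hypothesis. For superiority: "For the superiority hypotheses (e.g., efficacy outcomes for the FST), all analyses will be performed under the intention to treat principle". For non-inferiority: "We will follow best practice recommendations to perform non-inferiority analyses under the per-protocol principle". It adds that the per-protocol analysis will use inverse-probability weights from an attrition model fitted at 3 and 6 months.

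The Discussion identifies the endpoint this governs. It states "We selected 6-month survival as a safety outcome" and says the trial is meant to rule out "increased mortality in the intervention arm through non-inferiority testing".

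The Intervention section (2.5) sets out what the intervention arm has to do. Surrogates are prompted to complete FST section 1 on enrolment and sections 2 and 3 before the first meeting. Staff are "to schedule the first family meeting, within 2 days of enrollment". The second meeting is conditional: "If the patient remains in the ICU on study day 5". Later weekly meetings are conditional on ICU stay in the same way. The Standard care arm section (2.10) leaves communication and support to the treating clinicians, so that arm has no comparable steps.

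The Eligibility criteria (2.3) admit patients judged to have at least a 40% risk of death or at least a 40% chance of new severe impairment. They exclude patients expected to die within 24 hours, those already on comfort measures only, and those for whom withdrawal of life support has been decided.

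**The concern.** The usual argument for a per-protocol analysis in a non-inferiority trial is that non-adherence dilutes a true difference under intention to treat. That argument is safe only if adherence is unrelated to prognosis. Here, completing the first steps takes up to two days of survival after randomisation in a critically ill population, and only one arm has those steps. A per-protocol set defined by completed steps would therefore select on early outcome in the intervention arm and leave the control arm intact.

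The endpoint is mortality, and the Discussion gives the purpose of the test as addressing concern that supporting surrogates might shorten survival. If the comparison loses the protection of randomisation, a finding of non-inferiority could partly reflect who was left out. The attrition weights do not repair this, because they model loss to follow-up and not removal for failing to complete a step.

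**Working it through.** **The plan's own figure.** 370 × (1 − 0.20) = 296 patients, or 148 per arm. This reproduces. The article does not show the margin, alpha, power or event rates for the survival test, so that calculation cannot be reproduced.

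**Inputs**
- From the article: 370 randomised 1:1 (185 per arm); 296 after 20% loss (148 per arm); first meeting within 2 days; no steps in the usual-care arm.
- Assumed: 6-month mortality p of 40–60%; share e of the intervention arm that dies before the first meeting and is dropped, 3–8%; one-sided alpha 2.5%; margin 15 percentage points.

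**Step 1: bias when true mortality is equal.** Dropping a share e, all of whom died, changes intervention mortality from p to (p − e)/(1 − e). Control stays at p.

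| p | e = 3% | e = 5% | e = 8% |
|---|---|---|---|
| 40% | −1.9 | −3.2 | −5.2 |
| 50% | −1.6 | −2.6 | −4.3 |
| 60% | −1.2 | −2.1 | −3.5 |

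Entries are percentage points. Example: (0.40 − 0.08)/(1 − 0.08) = 0.348, which is 5.2 points below 0.40.

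**Step 2: false non-inferiority rate at the margin.** Set true mortality at 60% (intervention) and 45% (control), so that the true excess equals the 15-point margin. After exclusion, intervention mortality is (0.60 − e)/(1 − e), the apparent difference is d, and the rate is Φ((0.15 − d)/SE − 1.96). SE is unpooled, with n(1 − e) patients in the intervention arm and n in control.

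| e | d | 185 per arm | 148 per arm |
|---|---|---|---|
| 0 | 15.0 points | 2.5% | 2.5% |
| 3% | 13.8 | 4.3% | 4.0% |
| 5% | 12.9 | 6.0% | 5.5% |
| 8% | 11.5 | 9.7% | 8.5% |

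Example with e = 5% and 185 per arm: (0.15 − 0.1289)/0.0522 = 0.403, and Φ(0.403 − 1.96) = 6.0%. The e = 0 row is the analysis of all randomised patients.

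**Step 3: can the bias run the other way?** Suppose a share s of early survivors is also dropped, for example because they left the ICU or regained capacity before the meeting. Apparent mortality is then (p − e)/(1 − e − s). At p = 40%:
- e = 5%, s = 5%: −1.1 points
- e = 5%, s = 7.5%: 0
- e = 5%, s = 10%: +1.2 points
- e = 0, s = 5%: +2.1 points

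The sign therefore depends on who the per-protocol definition removes.

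**The case against.** The strongest reply is that the article does not define the per-protocol set, and that definition commonly sits in a statistical analysis plan. A reader might infer that the analysis will remove early deaths from the intervention arm and so favour declaring safety. The documents do not establish either part. Death before a meeting might be counted as adherent. The only mechanism the article attaches to the per-protocol analysis is attrition weighting, which also fits an analysis with no adherence exclusions. Step 3 shows that the direction is not fixed. This stands, and the point is worded as a possibility for that reason.

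The exposure window is also short. The day 5–9 meeting is required only of patients still in the ICU, so a patient who dies or leaves earlier has not missed it. The relevant period is at most the two days to the first meeting, in a population from which expected deaths within 24 hours are already excluded. The Background reports that 96% of pilot participants used the tool as planned. That figure concerns tool use and not meetings, but it suggests that the lower end of the 3–8% range is more plausible than the upper end.

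The article does not forbid an all-randomised survival analysis. Survival duration is listed in Table 2, secondary outcomes are to be compared between arms, and a DSMB monitors safety. Intention to treat alone can also be anti-conservative for non-inferiority, because undelivered intervention dilutes harm. That is a reason to require both analyses. It does not support relying on per-protocol alone.

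None of this removes the stated rule: the article names one principle for non-inferiority, and it is per-protocol.

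**Conclusion.** The point holds in a conditional form. The article fixes per-protocol as the principle for the survival non-inferiority test and names no all-randomised counterpart, for a mortality endpoint where adherence steps exist in one arm only. The attrition weights do not cover selection by adherence. If early deaths alone were excluded, apparent intervention mortality would be 1.2–5.2 points too low, and the false non-inferiority rate would be about 4–10% instead of 2.5%. These sizes rest on assumed early-death shares of 3–8%, mortality of 40–60%, one-sided alpha of 2.5% and a 15-point margin, none of which the article gives. Excluding early survivors as well would shrink, cancel or reverse the effect.

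A reader might also infer that the Discussion's claim of adequate power to rule out increased mortality is wrong. The documents do not support that, because the margin, alpha and event rates behind the claim are not shown.

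**What to change.** In the Statistical analysis plan section, state three things:
- Non-inferiority for 6-month survival will be analysed in all randomised patients as the primary or co-primary analysis, alongside the per-protocol analysis.
- Non-inferiority will be claimed only if both analyses meet the margin.
- For the per-protocol set, death or ICU discharge before a scheduled step is not non-adherence.

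This protects the conclusion whichever way the selection runs. It needs no new data collection, because Table 2 takes survival from chart abstraction. The cost is a change of wording and a slightly harder non-inferiority claim, since two analyses must agree.
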